## Abstract

**Background:**

Chronic Fatigue Syndrome is a debilitating disorder with an unknown aetiology but suspected multifactorial origins. Common “triggers” include severe viral infections and emotional stress. Recent studies have also found evidence of immune dysfunction and elevated inflammatory cytokines in CFS patients, but there has been considerable variation in the outcome measures and magnitude of these studies. Currently, there is no cure for CFS but treatments include rest, specialist medical care, cognitive behavioural therapy, and graded (self-paced) exercise. To date, several studies have examined the efficacy of graded exercise with or without Cognitive Behavioural Therapy, with some success for patients. However, improvements in functional capacity have not necessarily correlated with improvements in immune function, fatigue or other symptoms. This 12-week pilot trial compares graded and intermittent exercise to normal care, measuring physiological outcomes, fatigue levels, immune function and wellness.

**Methods/design:**

90 patients aged between 16 to 60 years, who meet the diagnostic criteria for CFS and have been diagnosed by their medical practitioner, will be randomly recruited into groups consisting of Intermittent exercise, Graded exercise and usual care (Control). The outcomes will be measured pre-study (Week 0) and post-study (Week 13). Primary outcomes are VO_2peak_, anaerobic threshold, peak power, levels of fatigue, immune cell (CD3^+^CD4^+^, CD3^+^CD8^+^, CD19^+^, CD 16^+^CD56^+^) concentrations and activation. Secondary outcomes include onset of secondary CFS symptoms (e.g. fever, swollen lymph nodes), wellness, mood and sleep patterns. Primary analysis will be based on intention to treat using logistic regression models to compare treatments. Quantitative data will be analysed using repeated measures ANOVA with a linear model, and Cohen’s effect size. Qualitative data such as participants’ responses (e.g. changes in mood and other reactions) following the exercise modalities will be read and sections demarcated. A code will be applied to each segment. A prevalence of codes will be considered thematically.

**Discussion:**

The results of the trial will provide information about the efficacy of intermittent and graded exercise compared to usual care (rest and lifestyle recommendations), contributing to the evidence for best-practice CFS management.

**Trial registration:**

Australia and New Zealand Clinical Trials Registry ACTRN12612001241820.

## Background

Currently there is no clear aetiology associated with Chronic Fatigue Syndrome (also known as Myalgic Encephalitis). The syndrome is characterised by persistent, disabling and/or recurring fatigue, not alleviated by rest, and with other symptoms such as muscle weakness and pain, swollen lymph nodes and fever, poor concentration and reduced quality of life [1,2]. A medical diagnosis is made when three of the following criteria from the Centre for Disease Control and Prevention’s modified case definition of CFS, have been met [3]:

(1) The individual has had severe chronic fatigue for 6 or more consecutive months and the fatigue is not due to ongoing exertion or other medical conditions associated with fatigue (these other conditions need to be ruled out by a doctor after diagnostic tests have been conducted).

(2) The fatigue significantly interferes with daily activities and work.

(3) The individual concurrently has 4 or more of the following 8 symptoms: post-exertion malaise lasting more than 24 hours; unrefreshing sleep; significant impairment of short-term memory or concentration; muscle pain; pain in the joints without swelling or redness; headaches of a new type, pattern, or severity; tender lymph nodes in the neck or armpit; a sore throat that is frequent or recurring.

These symptoms should have persisted or recurred during six or more consecutive months of illness and they cannot have pre-dated the fatigue.

CFS is often triggered by a severe viral infection, such as Epstein Barr virus [4]. There is also increasing evidence to suggest that CFS is also associated with immune system dysfunction, such as increased inflammatory cytokines and reduced lymphocyte activation [4-7]. CFS can cause severe interruptions to education or employment for patients, and the physical inactivity associated with the syndrome may increase the risk of other chronic conditions such as cardiac disease, metabolic conditions and cancer. Earlier studies found that the majority of individuals with CFS have slight to substantial improvement within 1.5 - 4 years with less than 10% reporting complete recovery [8,9]. Approximately 20-50% of adults with CFS demonstrate some improvement in the condition, although only 6% returned to levels of normal function [10,11]. Rehabilitation is usually slow with symptoms described as fluctuating. Approximately 10% of individuals with CFS may improve for periods of at least a year, with a proportion relapsing intermittently [10,11]. Most patients relate that they never return to their pre-morbid level of health [11,12]. After a period of rest, some individuals may return to work but usually with limited working hours. It is apparent that the combination of tiredness, poor memory and difficulties with concentration are reflected in the changes to their productivity.

CFS patients are often advised to remain as active as possible but patients usually show a range of physiological responses to exercise indicative of fatigue and deconditioning. Such responses include reduced exercise capacity, early onset of anaerobic threshold, increased lactate responses during incremental exercise, increased heart rate responses, and also anomalies within perception of their physical effort such as higher rates of perceived exertion compared to controls [2,13,14]. Hypothalamic, mitochondrial and sympathetic dysfunction may also be implicated in exercise and fatigue responses in CFS patients [3,15,16].

Strategies to manage CFS include pharmacology, physical activity where appropriate (for example graded exercise (GE) and pacing), and psychological approaches such as cognitive behavioural therapy (CBT) which seek to modify behaviour, beliefs and coping strategies. [17-20]. Current best practice for the physical training of CFS patients involves GE sessions where the patient exercises at a well-tolerated constant rate or load (steady state), and the duration of the exercise session is gradually increased over time [2,18-20]. CBT is usually combined with exercise management [18,20].

Evidence of the efficacy of GE, CBT, pacing and other prescriptions of physical activity has been mixed. Some CFS patients still report symptom exacerbation and muscle pain with GE, and consequently are less likely to be physically active [21,22]. Yet other studies have reported that aerobic and resistance exercise improves aerobic capacity and strength [13], fatigue [17], profile of mood states and inflammatory cytokines [14,17,21,23-26].

Intermittent training, where intervals of exercise are alternated with intervals of rest or very low intensity exercise, has been used with cardiac [27], pulmonary [28,29], cancer [30] and older clients who are very deconditioned [31]. Clapp et al. (1999) reported that an acute session of intermittent exercise for 30 minutes did not exacerbate CFS symptoms immediately post-exercise, or for up to 7 days post exercise [32]. In CFS patients, intermittent training may increase exercise tolerance by decreasing perceived exertion, and delaying the onset of fatigue and muscle pain, whilst still providing the same total amount of physical activity as GE. Patients may find it easier to adhere to an intermittent exercise programme if their symptoms are not exacerbated, and therefore may improve their health.

Study hypotheses and aims: the primary aim of the trial is to investigate the efficacy of 12 weeks of intermittent or graded exercise on aerobic capacity, fatigue, immune function and wellness in CFS patients compared to standard care (typically rest, pharmacology and advice about physical activity). We hypothesise that:

1) Both exercise interventions will improve exercise tolerance, aerobic capacity and wellness compared to the control condition, and

2) IE will result in greater exercise tolerance, less fatigue and other symptoms, improved immune function and better exercise adherence compared to GE.

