### Interventions

#### Exercise groups

Participants randomized to the exercise intervention groups will engage in a 12-week exercise program consisting of either intermittent exercise (IE) or graded exercise (GE). The exercise sessions will be group-based and conducted at the Southern Cross University Health Clinic, three times per week. All sessions will be supervised by an accredited Exercise Physiologist (AEP) and post-graduate clinical exercise physiology students. Each exercise session will consist of a 5 minute gentle warm up of unloaded cycling, followed by initially a 10 to 15 minute block of either steady state exercise (GE) or intermittent exercise (IE) at an intensity pre-determined from the baseline VO_2peak_ cycle test for each participant. Depending upon the symptom limits of the exercise, the duration of the exercise block can be gradually increased for each participant as tolerated to either a steady state (constant effort) low-moderate intensity cycling period, (50% VO_2peak_, RPE 3 [0–10 Borg Scale]) initially for 10 minutes (GE group) OR an intermittent exercise block of 1 minute of moderate intensity cycling (60% VO_2peak_, RPE 4–5) alternated with 1 minute of unloaded or very low intensity/unloaded cycling (20-30% VO_2peak_, RPE 1–2), totalling 20 minutes. A cool down of 5 minutes unloaded cycling plus stretching of main muscle groups for both groups is also included in the exercise session.

During the 12 weeks of training, we aim to progress the duration of GE towards 20 min, as tolerated by the participant, and to progress the IE participants towards intervals of 2–3 min of moderate intensity cycling, alternated with 1 minute intervals of low intensity cycling, totalling 25–30 min duration. Resting heart rate, heart rate variability (standard deviation of the normal to normal R-R intervals and the root mean square of differences of successive R-R intervals), resting blood pressure, RPE, (0–10 Borg Scale) and fatigue levels will be recorded prior to, and after, each exercise session. Participants will be asked to record any changes, such as elevated or depressed mood, changes to sleep patterns or general well-being, that they perceive to have occurred during their participation in the exercise training.

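### The Background says intermittent exercise gives the same total activity as graded exercise, but the target prescriptions do not match it and the starting durations conflict, so an IE–GE difference cannot be read as an effect of pattern at equal amount

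*Protocol article*

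**What the plan says.** In the Background, the argument for the intermittent arm is that it may improve exercise tolerance "whilst still providing the same total amount of physical activity as GE". Hypothesis 2 follows in the same section: IE is expected to do better than GE on tolerance, fatigue, other symptoms, immune function and adherence.

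The Exercise groups section (Methods, Interventions) then sets out the sessions:

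- **Opening block, both arms:** "initially a 10 to 15 minute block of either steady state exercise (GE) or intermittent exercise (IE").
- **GE:** "50% VO_2peak_, RPE 3 [0–10 Borg Scale]) initially for 10 minutes (GE group"), and later "we aim to progress the duration of GE towards 20 min".
- **IE:** the work interval is described as "intermittent exercise block of 1 minute of moderate intensity cycling (60% VO_2peak_, RPE 4–5"). The recovery interval between these efforts, and the length of the whole block, are given as "1 minute of unloaded or very low intensity/unloaded cycling (20-30% VO_2peak_, RPE 1–2), totalling 20 minutes". The aim over the 12 weeks is to lengthen the moderate intervals to 2–3 minutes, "alternated with 1 minute intervals of low intensity cycling, totalling 25–30 min duration".

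Session frequency, warm-up and cool-down are the same in both arms. Progression depends on what each participant tolerates.

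**The concern.** There are two conflicts. The equal-amount statement in the Background does not fit the different target durations and intensities in the Exercise groups section. Within that section, a common opening block of 10 to 15 minutes does not fit the arm-specific figures of 10 minutes for GE and 20 minutes for IE.

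They bear on the interpretation of the IE–GE contrast. The rationale offered for IE is a change of pattern at constant amount. If the amounts differ, a difference in VO2peak, fatigue or immune measures may reflect amount, pattern or both. The effect could go either way: more activity could add to a fitness gain under IE, or hide a tolerance, symptom or adherence advantage because IE participants are asked to do more. Randomisation does not separate the two, because the difference is built into the interventions.

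**Working it through.** **Metric.** The protocol does not define total amount of activity. I use the sum of minutes × %VO2peak over the main block, then vary the metric. The ratio implied by the Background is IE/GE = 1.00.

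**Inputs (Exercise groups section).** GE is at 50%, for 10 minutes initially and 20 at target. IE work intervals are at 60% and recovery at 20–30%. IE is 1:1 for 20 minutes in the arm-specific text, and 2:1 to 3:1 for 25–30 minutes at target. The progression text gives no new percentages, so I assume that 50%, 60% and 20–30% still apply at target.

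**Formulae.**
- GE = 50 × minutes.
- IE = T × (60w + r)/(w + 1), with T the total minutes, w the work-to-recovery ratio and r the recovery intensity.

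**Target, whole block.** GE = 50 × 20 = 1000.

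| Ratio | Recovery | Mean intensity | 25 min | 30 min |
|---|---|---|---|---|
| 2:1 | 20% | (120 + 20)/3 = 46.7% | 1167 | 1400 |
| 2:1 | 30% | (120 + 30)/3 = 50% | 1250 | 1500 |
| 3:1 | 20% | (180 + 20)/4 = 50% | 1250 | 1500 |
| 3:1 | 30% | (180 + 30)/4 = 52.5% | 1312.5 | 1575 |

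IE/GE is 1.17 to 1.58. The stated equality is not reproduced in any cell.

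**Target, other metrics.**
- Only the 60% intervals: 25 × 2/3 × 60 = 1000, up to 30 × 3/4 × 60 = 1350. Ratio 1.00 to 1.35.
- Minutes only: 25/20 to 30/20. Ratio 1.25 to 1.50.
- Adding 10 minutes of warm-up and cool-down at an assumed 20–30%: 1.14 to 1.44.
- Net of an assumed resting uptake of 10–20% VO2peak: 1.11 to 1.63.

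Equality appears only in one corner of the narrowest metric (60% intervals alone, 2:1, 25 minutes).

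**Start, whole block.** Mean IE intensity at 1:1 is (60 + 20)/2 = 40% to (60 + 30)/2 = 45%.
- Same 10 or 15 minute block in both arms: 40/50 to 45/50 = 0.80 to 0.90, so IE is 10% to 20% lower.
- GE 10 minutes, IE 20 minutes: 800/500 to 900/500 = 1.60 to 1.80, so IE is 60% to 80% higher.
- GE 15 minutes, IE 20 minutes: 800/750 to 900/750 = 1.07 to 1.20.

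The sign of the starting difference depends on which text is followed.

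**The case against.** The strongest reply has four parts.

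**The starting excess depends on a reading.** The 20-minute IE block stands in a sentence about increasing duration as tolerated, and the word for a starting value is attached only to GE ("initially for 10 minutes (GE group) OR an intermittent exercise block of 1 minute of moderate intensity cycling"). The 20 minutes may be a later step, with both arms opening at 10 to 15 minutes. This stands. A reader might join the two stages and infer that the protocol gives IE 17% to 80% more throughout. The documents do not support that: the upper end needs one reading of an unclear sentence, and the other reading puts IE lower.

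**The metric is not the protocol's.** The Background describes intermittent training as exercise intervals separated by rest or very light effort, so counting only the work intervals is fair. This stands too, and it is why the target excess is also given as 0% to 35%.

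**Hypothesis 2 does not name pattern as the cause.** A reader might infer that it credits any IE advantage to intermittency, or that the comparison is confounded and so invalid. Neither follows. Hypothesis 2 says only that IE will do better than GE, and the Design section compares two exercise programmes, a contrast that randomisation makes valid. Since progression depends on tolerance, and better tolerance and adherence are hypothesised IE effects, part of any delivered difference could itself be a result of treatment. What remains is that the rationale just before hypothesis 2 invites the equal-amount interpretation, and the different duration aims are set by the plan, whatever participants tolerate.

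**The statement is only background, worded as a possibility.** It is, and it is no matching rule in the Methods. It is nevertheless the stated reason for the intermittent arm, and the prescriptions do not deliver it.

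A session log of load and minutes is a detail that an article may leave to the full protocol. Its absence is not part of the finding.

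**Conclusion.** The point holds in a limited form. At target, IE is prescribed 17% to 58% more activity than GE on whole-block %VO2peak × minutes, or 0% to 35% more if only the 60% intervals count. At the start, the difference is undetermined: 10% to 20% less under one text, 60% to 80% more under the other. These are prescribed amounts. They assume that the stated intensities carry through to the target stage; delivered amounts may differ because progression is individual.

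The consequence is confined to interpretation of IE versus GE. A difference there can be read as a difference between two programmes, but not as an effect of intermittent pattern at equal amount. The comparison of exercise with usual care (hypothesis 1) is not affected.

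**What to change.** 1. Reconcile the equal-amount statement in the Background with the prescriptions in the Exercise groups section, and reconcile the two sets of starting durations within that section. Which of them is right is for the investigators to settle; this review takes no position.
2. If the prescriptions remain unequal, withdraw the equal-amount statement and word hypothesis 2 as a comparison of two programmes that differ in both pattern and amount.
3. Summarise delivered duration and load by arm from the supervised sessions, say which measure of amount is used, and limit the IE–GE conclusion to what that summary supports. Treat it as description: delivered amount arises after randomisation and may partly reflect treatment, so adjusting for it would not isolate pattern.

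The cost is some protocol wording, a small amount of data from sessions that are already supervised, and a narrower claim for IE over GE. Sample size and the comparison with control do not change.

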## Methods

### Design

This study is a randomised controlled trial that will compare the outcomes of a 12-week intermittent cycling exercise program to a graded exercise cycling program and standard care (rest and lifestyle advice). The primary outcomes of the study are aerobic capacity (VO_2peak_), perceived exertion, fatigue, muscle pain, immune cell counts, lymphocyte (CD4^+^, CD8^+^, CD19^+^, CD16^+^56^+^) concentrations and function. Secondary outcomes are wellness indices and physiological adaptations to exercise (changes in heart rate, heart rate variability, blood pressure, body composition, anaerobic threshold) and measures of presence, severity and type of fatigue (mental and physical). Southern Cross University Research Ethics Committee has approved all study procedures (HREC ECN-13-066).

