### Sample size and power calculation

A previous exercise intervention study provided VO_2peak_ data from a CFS sedentary, age-matched cohort (16.2±1.3 yr) [18]. This data has been used to compute statistical power *a priori* using the non-commercial statistical power analysis program G*Power. The control group is expected to experience no change in the aerobic capacity after 12-weeks while the intervention groups are expected to increase this measure following the exercise interventions. Setting an alpha level of 0.05, approximately 75 participants (25 per group) will provide 82% power to detect a statistically significant difference between groups. Recruitment will be inflated to 90 participants to enable a 20% participant attrition rate.

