#### Fatigue and muscle pain

RPE and fatigue will be recorded at rest and during the incremental exercise test. Participants will be asked to complete a linear pain scale (0 – 10) to indicate if they have any muscle or joint stiffness or soreness prior to the exercise test, immediately post-exercise and also 24 hours post-exercise test. RPE and pain scales will also be completed at every training session to carefully monitor symptoms. The Fatigue Severity Scale [34] and the Chalder Fatigue Scale [39], both CFS-specific, will be administered pre- and post-study to assess the severity and nature of the fatigue, mental and physical.

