### Statistical analyses

Primary analysis will be via intention-to-treat with all patients included regardless of dropout or level of adherence. Missing data will be imputed according to the maximum likelihood expectation algorithm via the Statistical Package for the Social Sciences (SPSS© Version 19.0). Physiological and exercise test data will be presented as the mean ± standard deviation, with confidence intervals used to express group differences. Changes between groups and the time effect for each group will be determined by repeated measures analysis of variance with a Bonferroni adjustment for significant differences between groups. Cohen’s Effect sizes and 90% confidence intervals will be calculated, to utilise a magnitude-based approach to inferences [41], with the following descriptors applied: (1) Effect size thresholds: <0.2 trivial, <0.6 small, <1.2 moderate, <2.0 large, <4.0 very large, >4.0 extremely large, and (2) Thresholds for assigning qualitative terms to chances of substantial effects: <0.5%, almost certainly not; <5.0%, very unlikely; <25%, unlikely; <75%, possible; >75%, likely; >95%, very likely; >99.5%, almost certain. An effect is unclear if its confidence interval includes both substantial increases and decreases [41]. A p value of < 0.05 will be considered indicative of statistical significance; clinical significance will be interpreted in light of the meaningfulness and magnitude of the adaptations observed. Data from linear pain scales will be recorded pre- and post-study, and reported as frequencies of scores between 0 and 10. Data will then be analysed using ANOVA (group and time effects). Data from wellness indices will be recorded pre and post, combined into domains and a representative total score from the time points analysed using an ANOVA. Data (non parametric) from the Fatigue scales, also measured at time points, will be collated and analysed using a Kruskall-Wallis test.

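### The abstract and the Methods give conflicting primary outcome lists, the primary fatigue measure is undefined, and about 9 to 14 variables share the label primary

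*Protocol article*

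**What the plan says.** The outcomes are ranked in three places in the protocol article.

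- **Abstract, Methods/design.** The primary outcomes are VO2peak, then "anaerobic threshold, peak power, levels of fatigue, immune cell" concentrations for four lymphocyte subsets, and activation. Wellness is secondary.
- **Methods, Design.** The primary outcomes are VO2peak, then "perceived exertion, fatigue, muscle pain, immune cell counts, lymphocyte" concentrations for four subsets, and function. The secondary list includes wellness indices, a group of physiological measures ending in "blood pressure, body composition, anaerobic threshold", and "measures of presence, severity and type of fatigue (mental and physical").
- **Background, hypotheses and aims.** The primary aim covers aerobic capacity, fatigue, immune function and wellness.

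Three other sections bear on the point.

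- **Fatigue and muscle pain** describes fatigue ratings taken at rest and during the incremental test, and separately two questionnaires: "The Fatigue Severity Scale [34] and the Chalder Fatigue Scale [39], both CFS-specific, will be administered pre- and post-study".
- **Sample size and power calculation** uses VO2peak data only: "Setting an alpha level of 0.05, approximately 75 participants (25 per group) will provide 82% power".
- **Statistical analyses** gives one threshold, "A p value of < 0.05 will be considered indicative of statistical significance", and one adjustment, "repeated measures analysis of variance with a Bonferroni adjustment for significant differences between groups".

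**The concern.** A trial's primary result is the one its sample size and error rate are meant to protect. Here a reader cannot tell from the article which variables hold that position. Both lists are current text, and they disagree on whether anaerobic threshold, peak power, perceived exertion, muscle pain and the general cell counts are primary. Fatigue is the defining symptom of the condition, yet nothing says which fatigue measure is the primary one.

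If this is left open until results are known, the choice of list can be influenced by them. Even with one list fixed, many variables would carry the label primary. The article gives no ranking among them and no rule for what counts as a positive trial.

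**Working it through.** **Step 1. Compare the lists.**

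| Variable | Abstract | Design section |
|---|---|---|
| VO2peak | primary | primary |
| Anaerobic threshold | primary | secondary |
| Peak power | primary | in neither list |
| Perceived exertion | not listed | primary |
| Muscle pain | not listed | primary |
| Immune cell counts (beyond the subsets) | not listed | primary |
| Four lymphocyte subset concentrations | primary | primary |
| Activation or function | primary | primary |
| Fatigue | primary (levels) | primary, with a further fatigue item secondary |
| Wellness | secondary | secondary, although in the primary aim |

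Shortening a list for an abstract can drop items. It cannot turn a secondary outcome into a primary one or add peak power.

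**Step 2. Count the primary variables.**

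- Abstract: VO2peak, anaerobic threshold, peak power and fatigue (4), plus 4 subsets, plus activation as one item = 9. With activation counted per subset: 4 + 4 + 4 = 12.
- Design: VO2peak, perceived exertion, fatigue, muscle pain and cell counts (5), plus 4 subsets, plus function as one item = 10. With function per subset: 5 + 4 + 4 = 13. With the two fatigue scales also counted separately: 14.

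The range is therefore 9 to 14, depending on how activation or function and fatigue are split.

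**Step 3. Chance of at least one false positive, no true effects, each variable tested at 0.05.**

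If the m tests are independent, the chance is 1 − 0.95^m:

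- m = 9: 1 − 0.630 = 37.0%
- m = 10: 1 − 0.599 = 40.1%
- m = 12: 1 − 0.540 = 46.0%
- m = 13: 1 − 0.513 = 48.7%
- m = 14: 1 − 0.488 = 51.2%

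The outcomes will be correlated, and the article gives no correlations. Values of 0.3, 0.5 and 0.8 were therefore assumed, equal for every pair. Three-group tests with 2 degrees of freedom were simulated 200,000 times for each setting:

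| m | 0.3 | 0.5 | 0.8 |
|---|---|---|---|
| 9 | 32.9% | 27.4% | 17.1% |
| 10 | 35.4% | 29.2% | 18.0% |
| 14 | 44.3% | 35.6% | 20.4% |

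**Step 4. What each remedy does to the stated power.**

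The 82% cannot be reproduced, because the article gives no effect size, SD or correlation. Working backwards, a one-way three-group ANOVA with 75 participants at alpha 0.05 reaches 82% at Cohen's f = 0.375. That value is implied under this test, not stated.

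- VO2peak as sole primary: alpha stays 0.05, so the 75-participant, 82% basis is unchanged.
- All variables kept as primary with Bonferroni: alpha per outcome is 0.05/9 = 0.0056 or 0.05/14 = 0.0036. At f = 0.375, power falls to about 53% or 47%. Restoring 82% takes about 120 or 129 evaluable participants.

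**The case against.** Four points can be made on the other side.

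- **Adjustment across outcomes may be set elsewhere.** Only a condensed article is shown, and an analysis plan could hold this rule. That stands, so the error rates are conditional on it. It does not remove the conflict between the lists, which is in the protocol's own text.
- **Fatigue may not be contradictory.** A reader might infer that the same outcome is flatly both primary and secondary. The documents do not support that. Under Design, primary fatigue sits beside perceived exertion, as the exercise-test ratings do in the fatigue section, while the secondary wording resembles what the two questionnaires assess. The two could be different measures. The article never says so, and the fair charge is that the primary fatigue measure is undefined.
- **The error rates could be read too strongly.** A reader might take 37% to 51% as the trial's false-positive rate. Those figures assume independence and no true effects, and several outcomes come from the same blood sample or the same exercise test. The correlated figures are lower but still more than three times 0.05.
- **The study calls itself a pilot and plans magnitude-based inference.** This softens the consequence, and no success rule is stated, so it goes too far to say the plan permits success to be claimed on any outcome. But the article also states an efficacy aim, directional hypotheses, 82% power and a significance threshold, and the pilot label does not say which list governs.

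**Conclusion.** The primary lists conflict and must be reconciled. That conclusion rests on the text alone and needs no assumption. Two related defects also stand: primary fatigue is not distinguished from the secondary fatigue item, and wellness is ranked differently in the aim and in the outcome lists.

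Multiplicity is a consequence of the unsettled lists and is less certain. With 9 to 14 primary variables and no true effects, the chance of at least one false positive is 37% to 51% under independence and about 17% to 44% under the assumed correlations of 0.8 to 0.3. This holds only if no adjustment across outcomes is specified in a document that is not shown.

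A reader might also infer that VO2peak is the only valid primary outcome. The documents do not go that far. It is the only outcome used for the sample size, but no section names it as sole primary and the stated aim is broader.

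**What to change.** Before any outcome data are seen:

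1. Put one identical primary list and one identical secondary list in the abstract and the Design section, and make the primary aim agree with them, including the place of wellness.
2. The simplest choice is change in VO2peak from baseline to Week 13 as the single primary outcome, since the existing alpha and power basis then needs no change.
3. State which fatigue measure is meant wherever fatigue is listed: the exercise-test ratings or a named scale.
4. Make the remaining outcomes secondary, for example with a Holm adjustment, or label them exploratory.
5. If several primaries are kept, or a different one is chosen, state the decision rule or the adjustment across outcomes and justify the sample size again on that basis.

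Steps 1 to 4 change wording only and need no further patients or data. The price is that fatigue, pain, exertion and the immune measures lose primary status, although several of them carry the hypothesis comparing intermittent with graded exercise. Step 5 could need a larger trial, as the Bonferroni figures in the working show.
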